***Laboratory analysis***

Collected samples will be transported to the central lab that is the Laboratory of Immunology and Infectious Diseases of the 4^th^ Department of Internal Medicine, ATTIKON University General Hospital, Athens, Greece. Analysis will be done as follows:

- PAXgene tubes or tubes with RNA*later*® for will be stored in -80°C for full transcriptomics
- EDTA tubes will be used: partly for direct isolation of peripheral blood mononuclear cells and further cytokine stimulation, partly for flow cytometry, and partly for whole blood immune functional assay. The remaining blood in EDTA tubes will be centrifuged and plasma will be stored in -20°C for metabolomics, cytokine analysis with enzyme immunoassay (EIA) and antibiotic concentration measurement with high-performance liquid chromatography (HPLC) in patients receiving meropenem, tigecyclin or colistin; leucocyte buffy coat remaining after plasma aspiration with sterile pipette will be equally stored in -20°C for genome analysis.
- Serum isolated from pyrogen and anticoagulant-free tube after centrifugation will be stored in -20°C to be used for metobolomic analysis and serum markers.
- Stool or rectal swab will be stored in -80°C, to be later processed for 16S rRNA sequencing of the intestinal microbiome.

***Cost analysis***

The cost of hospitalization associated with each intervention will be calculated in two ways, both of them from a National Health Service and personal social services perspective:

1. According to the first way, cost per day will be defined by the sum of multiplications of each counted item or resource (including administered antimicrobials, other drugs, fluids, blood products, any invasive procedure for source control, mechanical ventilation, renal replacement therapy, radiological examinations, insulin administered for standard glycemic control, enteral or parenteral nutrition) with its price in Euros (€) and the addition of the nominal cost of daily stay for the ICU or general ward. The unit price for each counted item will derive from the National Health Service tariff data official pricelist. The following are excluded from the analysis as their price is considered negligible and/ or equally distributed among groups: vitamins, reconstitution/ dilution fluids, electrolytes, catheter insertions, perfusion devices, monitoring devices, consumables such as laboratory testing, cleaning packs, gloves, or masks, echocardiography performed in ICU for monitoring purposes, transport costs at discharge, cost of human resources such as salary of nursing or medical personnel. Counting of the items will be performed from enrollment until discharge or day 28, by investigators completely blind to the allocated treatment.
2. According to the second way, the total cost of the index hospitalization (where enrollment took place) will be extracted from administrative hospital and insurance records, which are based on Diagnosis Related Groups (DRGs), a combination of ICD-10 diagnosis and codes of medical acts. This is completed by any additional cost of medication or medical equipment plus any extra bed-days per medical or surgical ward or ICU stay, for medications and bed-days exceeding the estimated length of stay per DRG.

Direct cost of additional medical care (e.g. new hospitalizations) up to 90 days will be recorded, if available.

***Cost-Effectiveness analysis***

The EuroCoL EQ-5D-3L^™^ questionnaire at 90 days (proxy and telephone version) data will be used to convert patient responses into Quality-Adjusted Life-Years (QALYs), to define patient-level perception of health-related quality of life on a 0,1 scale. Deceased patients will be counted as a 0 on that scale. Quality of life will be compared with the cost of hospitalization.

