- Evaluation of resolution of the infection and potential recurrence of infection according to the judgment of the attending physician
- Evaluation of potential adverse events

Visit 10 is on day 10. Procedures of this day include:

- Recording of SOFA score (see APPENDIX II); available blood cell count, biochemistry, coagulation times, urine output, blood gases, available radiological findings, clinically relevant microbiology and antimicrobial susceptibility testing, administered antimicrobials, other administered drugs and need for source infection control either by percutaneous interventions or by any operation.
- Survival status
- Evaluation of resolution of the infection and potential recurrence of infection according to the attending physician
- Sampling of 33 ml of venous blood; 9ml is collected into one pyrogen-free tube; and 24ml is collected into EDTA-coated tubes
- Evaluation of potential adverse events

Visits 11-28 are on days 11-28 respectively. They include

- Recording of SOFA score if available
- Administered antimicrobials, other administered drugs and need for source infection control either by percutaneous interventions or by any operation.
- Survival status
- Evaluation of resolution of the infection and potential infection recurrence according to the judgment of the attending physician
- Evaluation of potential adverse events

If the patient is discharged before day 28, a phone call will be performed on day 28 to assess survival status, need for new hospitalization or antibiotic therapy and potential adverse events. End-of-life decisions, if any, will be recorded.

Last visit: A phone call follow-up will be done on day 90 to assess survival status. If available, data concerning any new hospitalization, or antibiotic cure and potential adverse events will be collected during that phone call. Moreover, a self or proxy-assessment of health-related quality of life will be performed through the EQ-5D-3L^™^ questionnaire on the same visit (see APPENDIX IV) ^18^.

All information will be recorded on a specific paper Case Report Form (CRF).

The procedure to follow at each study visit is shown in APPENDIX V.

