**Secondary study endpoints**

To assess the effect of clarithromycin treatment compared to placebo treatment on the following:

- 28-day mortality in the subgroup of patients with septic shock
- All-cause 90-day mortality
- Early sepsis response, defined by an at least 25% decrease of day 1 SOFA score on day 3
- Sepsis resolution; this is defined by an at least 25% decrease of day 1 SOFA score on day 7
- New sepsis episode until day 28. A new sepsis episode is defined as a further increase of SOFA score by at least 2 points consequent to infection, in a patient who has experienced previous sepsis resolution (at least 25% decrease of day 1 SOFA score on day 7)
- Time until new sepsis episode. A new sepsis episode is noted in any patient who experiences any more than 25% decrease of day 1 SOFA score on day 7 and who has further increase of SOFA by at least 2 points, consequent to infection
- Biomarkers of sepsis-induced immunosuppression, through genome, metabolome, transcriptome, microbiome and cell population analysis
- The (primary) health economic outcome is cost per quality-adjusted life-year (QALY) gained for clarithromycin compared with placebo.

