**STATISTICAL ANALYSIS**

Qualitative endpoints will be analyzed by the Fisher’s exact test or continuity corrected Chi- square test, as appropriate. Logistic regression models will be used to evaluate variables associated with 28-day mortality. The effect on sepsis-induced immunosuppression will be a composite endpoint and it will result from the bioanalysis of gene expression, circulating cytokines and stimulated cytokines of patients. More precisely, bioanalysis of gene expression is anticipated to provide pathways modulated by treatment. These pathways will be validated by measurement of representative cytokines in cell supernatants. Comparisons of over-time changes will be done between the two groups of treatment. A p - value lower than 0.05 will be considered statistically significant, unless stated otherwise.

For the cost analysis, cost of each intervention will be counted and compared between groups, with non-parametric Mann-Whitney test, as previously described^10^. This analysis will be subject to robustness control to assess potential differences between different methods of cost calculation. Cost-effectiveness will be expressed as an incremental cost-to-effectiveness ratio (ICER) of clarithromycin compared with placebo, in a within-trial analysis (90 days). The ICER will be compared to a willingness-to-pay factor, which is either defined by the National Institute for Health and Care Excellence threshold or by per capita Gross Domestic Product. ^19, 20^

To evaluate the variation and significance of the ICER estimate, a bootstrapping method will be used.

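### The QALY in the health-economic endpoint is a day-90 utility score with no time weighting, and the cost window behind the ICER is not fixed

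*Supplement*

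**What the plan says.** Protocol version 2, Secondary study endpoints: "The (primary) health economic outcome is cost per quality-adjusted life-year (QALY) gained for clarithromycin compared with placebo". The SAP repeats this endpoint. Under General principles it leaves the whole cost-effectiveness analysis to a separate report and gives no QALY method.

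The only QALY rule is in the protocol's Cost-Effectiveness analysis section. The day-90 EQ-5D-3L data are to be converted into QALYs "to define patient-level perception of health-related quality of life on a 0,1 scale. Deceased patients will be counted as a 0 on that scale". The same section sets quality of life against the cost of hospitalisation.

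Under Study visits, the instrument is given once. At the day-90 call, "a self or proxy-assessment of health-related quality of life will be performed through the EQ-5D-3L" questionnaire. No baseline or day-28 value is planned.

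Under Statistical Analysis, the ICER is computed "in a within-trial analysis (90 days"), compared with a willingness-to-pay factor (a national-institute threshold or per-capita GDP), and its variation is assessed by bootstrap.

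The Cost analysis section gives two costings. For the first, "Counting of the items will be performed from enrollment until discharge or day 28". The second takes the total cost of the index admission from administrative records. Direct costs of further care up to day 90 are recorded where available.

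**The concern.** A utility at one time point is not a QALY. A QALY is utility accumulated over time lived, in years. The plan places each patient on a 0–1 scale at day 90 and calls the result QALYs, although the horizon is about a quarter of a year. It also scores a death on day 80 the same as a death on day 1.

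This matters because the ICER is compared with an external amount per QALY. If the denominator is in other units, that comparison has no clear meaning, and a conclusion on cost-effectiveness could change for that reason alone. Separately, if the numerator stops at day 28 while the effect is read at day 90, costs and effects cover different periods.

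**Working it through.** The documents state no QALY, ICER or conversion factor, so there is no figure of the plan's own to reproduce.

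**Inputs from the protocol.** Horizon 90 days (Statistical Analysis). One EQ-5D at day 90 (Study visits). Deaths scored 0 (Cost-Effectiveness analysis). Planning mortality 55% v 30% (Power calculation; the synopsis says this is at 28 days).

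**Assumptions, not in the documents.** Survivor utility u = 0.6 at day 90 (it cancels from every ratio below). Utility path before day 90 either constant or linear from 0. Mortality at day 90 as shown in the table. Deaths to day 28 either at constant hazard or all on day 1.

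**Step 1: one patient.**
- Largest possible accrual: 1 × 90/365.25 = 0.246 QALY.
- Survivor, constant utility: 0.6 × 0.2464 = 0.148, against 0.6 under the rule. Factor 365.25/90 = 4.06.
- Survivor, utility linear from 0: 0.148/2 = 0.074. Factor 2 × 4.06 = 8.1.
- Death on day 80, constant utility until death: 0.6 × 80/365.25 = 0.131, scored as 0.

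**Step 2: difference between arms.** The rule gives u × [S_T(90) − S_C(90)]. The time-weighted gain is the integral of u(t) × [S_T(t) − S_C(t)] over days 0–90, divided by 365.25.

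Worked case: constant hazard to day 28, no deaths afterwards, constant utility. Mean days lived over days 0–28 are 28 × (1 − S)/(−ln S).
- Placebo, S = 0.45: 28 × 0.55/0.7985 = 19.29 days.
- Clarithromycin, S = 0.70: 28 × 0.30/0.3567 = 23.55 days.
- Gap to day 28: 4.26 days. Days 28–90: 62 × 0.25 = 15.50 days. Total 19.76 days.
- Gain: 0.6 × 19.76/365.25 = 0.0325 QALY. Under the rule: 0.6 × 0.25 = 0.150. Ratio 4.6.

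Across the assumed scenarios:

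| Day-90 gap (assumed 90-day mortality) | Gain under the rule | Time-weighted gain | Ratio |
|---|---|---|---|
| 25 points (55% v 30%, or 65% v 40%) | 0.150 | 0.0181–0.0368 | 4.1–8.3 |
| 12.5 points (60% v 47.5%) | 0.075 | 0.0129–0.0300 | 2.5–5.8 |
| 5 points (65% v 60%) | 0.030 | 0.0094–0.0254 | 1.2–3.2 |
| 3 points (65% v 62%) | 0.018 | 0.0085–0.0241 | 0.75–2.1 |

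The ratio falls as the curves converge because the rule sees only the day-90 gap and discards the larger gap before it. Below 1, the rule understates the gain.

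**Step 3: effect on the ICER.** Illustration with an assumed EUR 1,000 incremental cost, u = 0.6 constant, and a 25-point gap throughout:
- Under the rule: 1,000/0.15 = EUR 6,667 per QALY.
- Time-weighted: 1,000/(0.15 × 0.2464) = EUR 27,056 per QALY.
- With −EUR 1,000 instead: −6,667 and −27,056. Both mean cheaper with a gain.

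**Step 4: cost windows against a 90-day effect.**
- Item costing: enrolment to discharge or day 28. It does not match.
- Administrative costing: the whole index admission, with no stated start at enrolment. Patients with hospital-acquired or ventilator-associated pneumonia are already in hospital when they qualify, so it may include days before randomisation.
- Further care to day 90: recorded if available, and not said to enter the ICER.

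Neither the Cost-Effectiveness analysis nor the Statistical Analysis section says which of these forms the numerator.

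**The case against.** The wording about converting responses into QALYs could cover a time multiplication that the authors left unsaid. That is possible, but the same sentence defines the result on a 0–1 scale, and the next puts deaths on that scale. At best the key step is unspecified.

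Four stronger readings are tempting, and the documents do not support them.

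- *The ICER is understated at least fourfold.* The 4.06 factor applies to a survivor at constant utility. It is not a floor for the difference between arms, as the table shows, and the protocol gives no day-90 gap.
- *The error always favours clarithromycin.* That needs a positive incremental cost. The protocol's Introduction reports savings in both prior trials: EUR 7,000 per surviving patient in one, and a median of EUR 1,000 per patient in the other. With lower cost and a QALY gain, rescaling does not change the sign. Scoring late deaths as 0 can also work against an arm that delays death.
- *Costs stop at day 28.* This is true of the first costing only. The second has no such cut, and a robustness check between methods is planned. The gap is that no base case is named. The effect of truncation cannot be computed from the documents.
- *The Mann-Whitney test undermines the ICER.* It is assigned to the separate cost comparison; the ICER is already to be bootstrapped.

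It is also fair to say that this is a secondary endpoint, to be reported separately. That limits the scope of the point but does not mend the rule.

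**Conclusion.** The point holds for the effect measure. The only QALY rule in the current documents, followed literally, does not give QALYs over the stated horizon. It overstates a survivor's QALYs about 4.06-fold at constant utility and about 8-fold if utility rises linearly from 0, and it ignores time lived before death.

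For the gain between arms, the factor is about 4 to 8 if a 25-point survival gap persists to day 90. It is smaller, and may fall below 1, if the curves converge. Understatement of the ICER against the willingness-to-pay factor follows only with a positive incremental cost and a persisting gap. These sizes rest on the planning mortality and on assumed utility paths and day-90 mortality.

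The cost window of the ICER is unspecified, and one of the candidate windows does not match the 90-day effect.

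The point concerns the secondary health-economic endpoint alone and should be settled before that report is analysed. The primary endpoint is untouched.

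**What to change.** - **QALYs.** Define them as the area under survival times utility over days 0–90, in years: 0 from the date of death and, for survivors, a stated path to the day-90 value. One option is linear from 0 at day 0, with constant day-90 utility as a sensitivity analysis.
- **Dates of death.** Record the date of death at the day-28 and day-90 calls. Daily follow-up covers in-hospital deaths to day 28, but the calls list survival status only.
- **Costs.** Name one base-case costing that runs from enrolment towards day 90: index-stay costs from enrolment plus recorded later care, with the 28-day item costing as a sensitivity analysis. State how unavailable later costs are handled.
- **ICER.** State that the bootstrapped ICER already planned uses differences in mean cost and mean QALYs.

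The cost is protocol or SAP wording, analysis code and one added item on the two calls. There are two drawbacks. The ICER may look less favourable, and the utility path before day 90 remains an assumption because EQ-5D is measured only once. Later care recorded only where available will also leave the 90-day cost incomplete for some patients.

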**STUDY ENDPOINTS**

**Primary study endpoint**

To assess the impact of intravenously administered clarithromycin as adjunctive treatment to standard antibiotic therapy compared to placebo on all-cause 28-day mortality.

**Secondary study endpoints**

To assess the effect of clarithromycin treatment compared to placebo treatment on the following:

- 28-day mortality in the subgroup of patients with septic shock
- All-cause 90-day mortality
- Early sepsis response, defined by an at least 25% decrease of day 1 SOFA score on day 3
- Sepsis resolution; this is defined by an at least 25% decrease of day 1 SOFA score on day 7
- New sepsis episode until day 28. A new sepsis episode is defined as a further increase of SOFA score by at least 2 points consequent to infection, in a patient who has experienced previous sepsis resolution (at least 25% decrease of day 1 SOFA score on day 7)
- Time until new sepsis episode. A new sepsis episode is noted in any patient who experiences any more than 25% decrease of day 1 SOFA score on day 7 and who has further increase of SOFA by at least 2 points, consequent to infection
- Biomarkers of sepsis-induced immunosuppression, through genome, metabolome, transcriptome, microbiome and cell population analysis
- The (primary) health economic outcome is cost per quality-adjusted life-year (QALY) gained for clarithromycin compared with placebo.

**POWER CALCULATION**

This is done for the primary study endpoint. We are planning a study of independent cases and controls with 1 control per case. Prior data indicate that the mortality among placebo-treated patients with sepsis and respiratory dysfunction was 55% and that this was decreased to 30%^11^. We need to study 55 subjects into each group to be able to reject the null hypothesis that the failure rates for both groups are equal with probability (power) 0.8. The Type I error probability associated with this test of this null hypothesis is 0.10. We will use a continuity-corrected chi-squared statistic or Fisher’s exact test to evaluate this null hypothesis.

**STATISTICAL ANALYSIS**

Qualitative endpoints will be analyzed by the Fisher’s exact test or continuity corrected Chi- square test, as appropriate. Logistic regression models will be used to evaluate variables associated with 28-day mortality. The effect on sepsis-induced immunosuppression will be a composite endpoint and it will result from the bioanalysis of gene expression, circulating cytokines and stimulated cytokines of patients. More precisely, bioanalysis of gene expression is anticipated to provide pathways modulated by treatment. These pathways will be validated by measurement of representative cytokines in cell supernatants. Comparisons of over-time changes will be done between the two groups of treatment. A p - value lower than 0.05 will be considered statistically significant, unless stated otherwise.

For the cost analysis, cost of each intervention will be counted and compared between groups, with non-parametric Mann-Whitney test, as previously described^10^. This analysis will be subject to robustness control to assess potential differences between different methods of cost calculation. Cost-effectiveness will be expressed as an incremental cost-to-effectiveness ratio (ICER) of clarithromycin compared with placebo, in a within-trial analysis (90 days). The ICER will be compared to a willingness-to-pay factor, which is either defined by the National Institute for Health and Care Excellence threshold or by per capita Gross Domestic Product. ^19, 20^

To evaluate the variation and significance of the ICER estimate, a bootstrapping method will be used.

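### The stand-alone cost comparison uses Mann-Whitney, which does not test mean cost; if deaths are much cheaper than survivals and survivors cost less on clarithromycin, it can mislead on cost

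*Supplement*

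**What the plan says.** Protocol version 2, Statistical analysis: "cost of each intervention will be counted and compared between groups, with non-parametric Mann-Whitney test", with significance at p < 0.05. The one check attached to this comparison is "This analysis will be subject to robustness control to assess potential differences between different methods of cost calculation", which varies how cost is built up and leaves the test unchanged.

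The Cost analysis section takes a health-service perspective and gives two methods. The first counts priced items from enrolment to discharge or day 28. Under the second, "the total cost of the index hospitalization (where enrollment took place) will be extracted from administrative hospital and insurance records"; no day-28 limit applies to it.

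Under Secondary study endpoints, "The (primary) health economic outcome is cost per quality-adjusted life-year (QALY) gained for clarithromycin compared with placebo". It is reported as a 90-day within-trial ICER, and "To evaluate the variation and significance of the ICER estimate, a bootstrapping method will be used". No mean cost difference with a confidence interval is specified for the cost comparison itself.

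The SAP names no cost test. Its General principles defer the whole cost-effectiveness analysis to a separate report and treat all secondary outcomes as exploratory. The protocol's Mann-Whitney therefore stands.

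**The concern.** From a payer's viewpoint the relevant quantity is mean cost per patient, and the difference in means is the numerator of the ICER. The Mann-Whitney null is that a patient drawn from one arm is equally likely to cost more or less than one drawn from the other. The two questions coincide when the arms differ by a pure shift.

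A shift is unlikely here. Each arm's cost is a mixture of patients who die and patients who survive, and the plan expects the mixing proportion to change: "mortality among placebo-treated patients with sepsis and respiratory dysfunction was 55% and that this was decreased to 30" per cent. Counting stops at death, so early deaths may be cheap. Moving patients from cheap deaths to dearer survivals changes the ranks even when savings among survivors hold the mean constant or lower it. The report could then carry a cost p-value that contradicts the incremental cost in its own ICER.

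**Working it through.** **Inputs from the documents.** Deaths 55% on placebo and 30% on clarithromycin; "We need to study 55 subjects into each group" (Power calculation); two-sided 5% level (Statistical analysis; SAP General principles).

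**The plan's own figure.** At two-sided α = 0.10 and 80% power:

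n = [1.645·√(2·0.425·0.575) + 0.842·√(0.55·0.45 + 0.30·0.70)]² / 0.25² = 47.3.

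With continuity correction, n/4·[1 + √(1 + 4/(0.25n))]² = 55.0. The stated 55 per arm is reproduced. No figure is stated for the cost comparison.

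**Assumed, because the documents give no cost distribution.** Let r be mean decedent cost divided by mean placebo-survivor cost, from 0.1 to 1.0. Costs are gamma or lognormal, with coefficient of variation 1.0 in decedents and 0.7 in survivors. Decedent cost is the same in both arms.

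**Construction.** Set placebo-survivor cost to 20 units. The placebo mean is 0.55·20r + 0.45·20. For a mean saving s, clarithromycin survivors must cost [(1−s)·placebo mean − 0.30·20r]/0.70. For r = 0.2:
- Placebo mean: 0.55·4 + 0.45·20 = 11.2.
- Equal means need survivors at (11.2 − 1.2)/0.70 = 14.3.
- A 30% saving needs (7.84 − 1.2)/0.70 = 9.5.
- If survivors stay at 20, the clarithromycin mean is 0.30·4 + 0.70·20 = 15.2, which is higher than placebo.

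So when deaths are cheaper than survivals, equal means, and any saving, require cheaper survivors on clarithromycin.

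**Rejection rates, 10,000 trials per cell, gamma / lognormal, in %:**

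| r | Equal means: Mann-Whitney | Equal means: Welch t | 30% saving: Mann-Whitney | 30% saving: Welch t |
|---|---|---|---|---|
| 0.1 | 21.3 / 22.7 | 5.1 / 5.5 | 6.3 / 6.1 | 29.3 / 30.2 |
| 0.2 | 14.6 / 15.1 | 5.1 / 5.2 | 7.6 / 9.0 | 40.1 / 41.3 |
| 0.3 | 9.7 / 10.8 | 5.1 / 4.4 | 15.6 / 18.3 | 47.1 / 48.7 |
| 0.4 | 7.0 / 8.4 | 5.0 / 4.7 | 24.9 / 33.2 | 52.3 / 55.6 |
| 0.6 | 6.1 / 6.6 | 4.9 / 5.1 | 40.3 / 55.2 | 57.3 / 60.3 |
| 1.0 | 5.3 / 5.7 | 4.7 / 4.8 | 52.3 / 72.9 | 53.3 / 57.2 |

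**Direction (gamma, r = 0.2).** At equal means, 14.3 of the 14.6 points of rejection call clarithromycin dearer. With a true 20% saving, Mann-Whitney rejects 5.6% of the time, and 3.1 of those points are in the wrong direction.

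**Control.** With identical mortality and identical cost distributions, Mann-Whitney holds 5%.

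**Other uncapped runs.** Further gamma runs at r of about 0.1-0.3 gave 9-24% rejection at equal means. For a 25% saving, power was 5-16% by Mann-Whitney against 19-46% for a test of means.

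**Day-28 cap (first costing method).** These runs assume cost proportional to stay, deaths at a mean of 4-12 days and placebo survivors at 25-50 days. Size stays near nominal. Power falls by 20-45 points in most saving scenarios (mean 10.2 vs 13.7 days: 26% vs 64%) and by 12-16 points in the rest.

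**Bootstrap of the mean difference.** Size was 5-6% at r = 0.2 and 0.3 (600 trials) and 6-7% in the stay-based runs. Power for a 30% saving was 42% at r = 0.2 and 56% at r = 0.3.

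**The case against.** A reader might infer that the expected mortality difference is enough on its own to make Mann-Whitney both raise false cost signals and miss real savings. The documents do not support that. Both failures also need deaths to be far cheaper than survivals and survivors to cost less on clarithromycin, and neither is quantified. The nearest evidence is the Introduction's report that the first trial saved 7000 euros per surviving patient. That fits cheaper survivors, but it could also mean total cost divided by survivors.

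The protocol's costing may also raise r. The second method is DRG-based and covers the whole index stay, including days before enrolment. The first method prices ICU and ward days separately, and decedents' days may be the dearer ones. Illustrative runs at equal means show the effect. They assume an ICU day at 3 times a ward day, decedents always in ICU, survivors there for 40% of days, and 10-12 pre-enrolment days:
- Deaths at 8 days and survivors at 35: rejection falls from 12% to 7% with ICU pricing, and to 5.5% with pre-enrolment days added.
- Deaths at 12 days and survivors at 25 (ratio 0.48): it is about 6% even with cost proportional to stay.
- Deaths at 4 days and survivors at 50: it stays at 10-21%.

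With skewed costs and r near 1, Mann-Whitney can be the more powerful test (73% vs 57% in the table). If survivors' costs are unchanged, the two tests perform similarly.

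A reader might also infer that the cost-effectiveness conclusion is unsound. It is not: the ICER uses mean costs and has its own bootstrap.

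These points limit the size and reach of the problem. They do not make a rank test a test of mean cost. The wording is also loose, since the cost of each intervention can be read as component costs rather than total cost per arm; the plan should say which is meant.

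**Conclusion.** The point holds conditionally, for the stand-alone cost comparison only. Mann-Whitney answers a different question from the ICER beside it, and the planned robustness check does not vary the test.

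The harm is material if r is about 0.3 or below, mortality moves as planned and survivors cost less on clarithromycin. False signals of higher cost then occur in roughly 9-24% of trials at nominal 5% (uncapped cost), and power for a 25% saving is about 5-16% rather than 19-46%. At r of about 0.5 or more the error at equal means is near nominal, though with gamma costs some power is still lost at 0.6 (40% vs 57% for a 30% saving). Under the 28-day cap the harm is mainly lost power.

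All these sizes rest on assumed cost distributions. This is an inexpensive improvement to a secondary, exploratory analysis, not a defect in the primary health-economic outcome.

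**What to change.** In the protocol's Statistical analysis section, or in the plan for the separate cost-effectiveness report, state that the primary cost comparison is the difference in arithmetic mean total cost per randomised patient, clarithromycin minus placebo. Give it a bootstrap 95% CI, under both costing methods, from the same patient-level resamples as the ICER. Mann-Whitney, with medians and quartiles, may stay as a description of the distributions, but no conclusion on cost should rest on it.

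The change costs one sentence, because the bootstrap is already planned. Two downsides should be accepted openly: the mean is more sensitive to a few very expensive stays, and the bootstrap interval's error rate is slightly above 5% at this sample size (5-7% in the runs above).
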